### Inclusion and exclusion criteria

Inclusion criteria

• Patients suitable for curative surgery ≤ 80 years old

• Histhopatological confirmed gastric cancer (adenocarcinoma)

• Informed consent

Exclusion criteria

• Informed consent refusal

• Previous cholecystectomy

• Demonstrated cholelithiasis or biliary sludge

• Metastatic disease

• Metabolic diseases that may favour gallstones formation (hemolytic anemia, genetic hypercholesterolemia)

### Intervention

Preoperative data collection will include patient demographics and comorbidities (genitourinary, cardiac, pulmonary, gastrointestinal, renal, or rheumatologic).

The standard surgery for gastric cancer includes both total and subtotal gastrectomy with lymphadenectomy (D1, D2, D3), either laparoscopic or laparotomic. All types of reconstructions are allowed, including either mechanic or hand-sewn anastomosis. The standard open or laparoscopic cholecystectomy includes Calot's dissection with the cystic duct and artery ligated prior removal. The fundus-first technique is also allowed. Drainage tubes are left on routine basis, and withdrawn according to surgeon's preference.

### Data Collection

Patients' data files are generated containing demographic data and preoperative, operative, and postoperative information.

Pre-operative notes concern the history of gastric symptoms, the presence of associated diseases (cardiac, hypertension, diabetes, malignancy), duration of complaints (as an indication for the onset of the disease), and laboratory results of WBC count, serum bilirubin, gamma GT, and alkaline phosphatase. Ultrasound preoperative exclusion of gallbladder diseases is mandatory.

Operative data of concern are confirmation of a normal gallbladder, type of gastrectomy (subtotal or total), extent of lymphadenectomy (D1, D2 and 12^th ^node station, D3) and reconstruction. Postoperative notes of interest include the use of Total Parenteral Nutrition (TPN) or Enteral Nutrition (EN), complications, and length of hospital stay. Laboratory tests of WBC count, serum bilirubin, gamma GT, and alkaline phosphatase are also collected in postoperative days 3^rd ^and 7^th^.

Complications are classified as surgical infections (wound infection, subphrenic or subhepatic abscesses); noninfectious surgical problems (e.g. anastomotic leakage, bile duct injury, hemorrhage); remote infections (urinary or respiratory); and miscellaneous problems (e.g. pulmonary complications, deep venous thrombosis, cardiac complications, etc). The collected information are entered into a database as either continuous or categorical variables for statistical analysis.

A second surgeon (different from the one who participating in the intervention), aware of the operative findings but not the management of the gallbladder, will then assume the care of the patient. Postoperative care and ability to be discharged from the hospital will be determined by the second surgical team. This second surgical team will be blinded to the treatment of the gallbladder. The primary operative team will be in every moment available for emergent consultation.

Patient discharge will be based on good medical practice criteria: 1) apyrexia 2) absence of diseases requiring hospitalisation 3) light meals tolerance 4) return of bowel function 5) patient's compliance. A routine ultrasonography of hepathobiliary region will be scheduled after 4 and every 6 months for the first two years and yearly for the rest of the follow-up (at least 5 years) to assess possible cholelithiasis development. Routine blood check with specific hepatic tests will be collected with the same schedule. Routine oncologic follow-up in an outpatient setting are also added according to current protocols.

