### Statistics

#### Power Calculations

To compute sample size, the proportion of patients free from cholelithiasis was assumed to be 100% 5 years after gastrectomy plus prophylactic cholecystectomy. It is known from the current literature that the cumulative incidence of cholelitiasis 5 years after gastrectomy is around 15–25% while in the general population 5 years cumulative incidence is around 5% [1-4]. The 5-yr cumulative incidence of cholelithiasis after cholecystectomy is known to be null. Hence we assumed a 5 years cumulative incidence of 20% in patients undergoing gastrectomy alone and of 0% in patients undergoing gastrectomy + cholecystectomy.

Gastrectomy with concomitant cholecystectomy was assumed to increase cholelithiasis-free survival from 80% to 100%. Assuming a constant accrual rate and an accrual time of 2 years, a minimum follow-up period of 3 years, an overall survival probability of 50% at 5 years, 122 patients (61 in the control group and 61 in the cholecystectomy group) are necessary to ensure an 80% power with an alpha of 5%, when using a two-sided log-rank test.

Assuming a 50% drop-out rate during a 3 years follow-up allows to account for both cancer mortality and follow-up loss. These assumptions were based on the fact that competing events (deaths) will be substantial while patients lost from follow-up will be few. In a GIRCG series of 1032 patients undergoing gastrectomy plus lymphadenectomy 3 years disease-related survival was 59% (95% CI 41–60%), while no patient was lost to follow-up in the first 3 years after gastrectomy[15]. Therefore, to be conservative, we assumed a 50% loss during a follow-up period of three years, to account for both cancer mortality and loss to follow-up.

The statistical power sample calculation was carried out using PASS 2005 (Power Analysis and Sample Size, within the statistical package "NCSS 2004 and PASS 2005")[16] (see additional file 1).

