#### Tests

To evaluate significance of differences between the two groups, chi-squared and Fisher's exact test will be used as appropriated for categorical variables, and the non-parametric Mann-Whitney U-test for continuous variables. To evaluate differences in the incidence of cholelithiasis, Kaplan-Meier survival curves will be computed considering as endpoint the onset of cholelithiasis itself. Survival curves will be compared by log-rank test and multivariable analysis will be accomplished by the Cox regression model. Significance level will be set at 5%. The statistical analysis will be carried out using the Statistical Package for the Social Sciences (SPSS version 13; SPSS Inc. Chicago, Illinois, USA).

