#### Primary aims of the study

The aim of the study is to compare the results of gastrectomy plus prophylactic cholecystectomy versus gastrectomy only in patients undergoing gastric cancer surgery with a curative intent, in terms of morbidity, mortality, operation time, hospital stay, postoperative pain, return to normal activity, quality of life, and development of biliary symptoms after 5 years from surgery.

The primary aims of our study will be:

A) To evaluate whether patients who had not a prophylactic cholecystectomy and developed cholelithiasis will eventually suffer from symptoms related to their gallstones and will need another surgical intervention 5 years after gastrectomy

B) To evaluate the incidence of cholelithiasis in patients who have undegone gastric surgery

C) To evaluate whether prophylactic cholecystectomy increases complications rate, operative time and postoperative stay.

The onset of any other complications will be recorded intraoperatively, postoperatively, at discharge, 4-months after surgery. Subsequently, visits will be scheduled every 6-months in first two years after surgery, and yearly thereafter till completion of the 5-year follow-up.

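### A stone missed at entry is removed unseen in the cholecystectomy arm but can be counted as new onset in the control arm; recording stones in the removed gallbladders would bound this cheaply

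*Protocol article*

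**What the plan says.** All references are to the protocol article.

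- **Inclusion and exclusion criteria.** The relevant exclusion is "Demonstrated cholelithiasis or biliary sludge". Undetected disease does not exclude a patient.
- **Data Collection, preoperative.** "Ultrasound preoperative exclusion of gallbladder diseases is mandatory".
- **Data Collection, operative.** The list opens with "Operative data of concern are confirmation of a normal gallbladder, type of gastrectomy (subtotal or total" and goes on to lymphadenectomy and reconstruction. It does not say how normality is confirmed. The postoperative items go down to blood tests on days 3 and 7, but no finding from the removed gallbladder is listed.
- **Intervention.** "The standard open or laparoscopic cholecystectomy includes Calot's dissection with the cystic duct and artery ligated prior removal". The organ is therefore available in the cholecystectomy arm.
- **Data Collection, follow-up.** "A routine ultrasonography of hepathobiliary region will be scheduled after 4 and every 6 months for the first two years". The first postoperative look is at 4 months.
- **Tests.** "Kaplan-Meier survival curves will be computed considering as endpoint the onset of cholelithiasis itself".
- **Primary aims, B.** "To evaluate the incidence of cholelithiasis in patients who have undegone gastric surgery". Aim A follows control patients in whom stones developed and asks whether they come to symptoms or further surgery.

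**The concern.** Randomisation balances missed stones between the arms at entry, but not what happens to them afterwards. After cholecystectomy they are gone and can never be events. After gastrectomy alone they stay in place, and the first scan that shows them dates them as onset. The control-arm curve then mixes stones already present with stones formed after surgery.

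Aim B, which reports that incidence, is overstated. The group studied under aim A may also include patients whose stones predate the operation. Few events are expected, so even a small number of missed stones is a visible share of the total.

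The cholecystectomy arm is a random half of the entrants, and its gallbladders are removed at time zero. They can show how common undetected stones were at entry, but the stated data list does not use them.

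**Working it through.** **1. Inputs from Power Calculations.** The assumed event rates are: "Hence we assumed a 5 years cumulative incidence of 20% in patients undergoing gastrectomy alone and of 0% in patients undergoing gastrectomy + cholecystectomy". Also stated: 50% overall survival at 5 years, 2 years of accrual, at least 3 years of follow-up, 61 patients per arm, 80% power, and a two-sided log-rank test at 5%.

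**2. The plan's own figure.** With no events in one arm (hazard ratio 0), Freedman's formula needs (1.960 + 0.842)² = 7.85 events. Take exponential stone onset and exponential death, with uniform accrual and 3 to 5 years of follow-up. The control-arm probability of an observed stone is then 0.1259. The total is 2 × 7.85 / 0.1259 = 124.7, close to the stated 122.

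**3. Expected control-arm events by 5 years.**
- Stone hazard: −ln(0.8)/5 = 0.0446 per year.
- Death hazard: ln(2)/5 = 0.1386 per year.
- Probability of an observed stone: 0.0446/(0.0446 + 0.1386) × (1 − 0.8 × 0.5) = 0.146.
- Expected events: 61 × 0.146 = 8.9. With 3 to 5 years of follow-up the figure is 61 × 0.1259 = 7.7.

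**4. Effect of missed stones.** Let q be the share of entrants with a stone missed at entry. The documents give no value, so q = 1% to 5% is an assumption. Assume also that each carrier alive at 4 months is detected then. Survival to 4 months is 0.5^(1/15) = 0.955. Expected events are 61 × [(1 − q) × 0.146 + q × 0.955].

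| q | Carriers among 61 | Expected events | Increase over 8.9 |
|---|---|---|---|
| 1% | 0.6 | 9.4 | about 6% |
| 5% | 3.1 | 11.4 | about 28% |

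The relative increase equals q × (0.955/p − 1), where p is the probability of an observed stone. With p = 0.1259 (3 to 5 years of follow-up) it is about 7% to 33%.

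**5. The same effect on the 5-year cumulative incidence.**
- If true new onset is 20%, the observed figure is 1 − (1 − q) × 0.8, which is 20.8% at q = 1% and 24.0% at q = 5%.
- If the observed figure is 20%, true new onset is 1 − 0.8/(1 − q), which is 19.2% and 15.8%.

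**6. Power.** Log-rank tests were simulated with 61 per arm and the observed 5-year rate held at 20%. When only new-onset stones count, power is 92% at q = 2% and 84% at q = 5%. Both exceed the planned 80%.

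**7. What 61 specimens can show.** With no stones found, the upper one-sided 95% limit is 1 − 0.05^(1/61) = 4.8%. Exact two-sided 95% intervals are 0 to 5.9% for 0 of 61, 0.04% to 8.8% for 1 of 61, and 1.0% to 13.7% for 3 of 61.

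**The case against.** **This is a condensed article.** Specimen pathology may be routine or set out in the full protocol, and nothing in the text is contradictory or miscalculated on this point. That stands, and it makes this an improvement and not an error. What remains is that the stated exclusion, endpoint and data list together make no use of evidence the design produces anyway.

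**Two checks already guard entry.** The ultrasound and the operative confirmation do reduce the problem. They cannot show how much is left.

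**Stronger readings that the documents do not support.**
- *The arm comparison or the sample size is compromised.* It is not. A stone left in place is part of what omitting cholecystectomy means, so the contrast of policies is valid, and power holds in the cases simulated.
- *Aim B claims incidence caused by gastrectomy.* Its wording is incidence in patients who had gastric surgery. No cause is stated.
- *Every missed case adds one event.* That would give 0.6/8.9 to 3.05/8.9, or 7% to 34%. Some carriers would have formed stones anyway and some die before the first scan, hence 6% to 28%.
- *Missed sludge is counted too.* The exclusion names sludge, but the endpoint names only cholelithiasis.
- *The excess must cluster at 4 months.* The method that missed a stone before surgery may miss it again.

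**The remedy is imperfect.** An opened specimen can show stones that ultrasound would never detect. Some stones seen at 4 months are genuinely new. With 0 of 61, nearly all of the assumed 1% to 5% range stays open. All of this stands, and it is why the result should inform a sensitivity analysis and not a correction.

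**Conclusion.** The point holds as a cheap improvement. Stones missed at entry cannot become events in the cholecystectomy arm but can be counted as onset in the control arm, so the aim B incidence is biased upward and the aim A stone group may include pre-existing disease. The direction is clear. The size is not known, because the documents give no miss rate.

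The range of roughly 6% to 28% more events, over about 9 expected, rests on four assumptions: 1% to 5% missed stones, the plan's 5-year rates, exponential onset and death, and detection of surviving carriers at 4 months. The two-policy comparison, the log-rank test and the target of 122 need no change.

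**What to change.** 1. Add to the data list in Data Collection: *stones in the opened gallbladder specimen (cholecystectomy arm): yes/no*. Record sludge in a separate field. Withhold both from the blinded second surgical team, since the entry itself reveals the allocation.
2. Report the stone prevalence with an exact confidence interval, as an indication of undetected disease at entry.
3. For aim B, add one sensitivity estimate that treats control-arm stones first seen at the 4-month scan as possibly prevalent and does not count them as onset. Show it beside the main estimate.
4. Keep every patient and the main analysis unchanged. Do not subtract a pooled stones-or-sludge prevalence from the control-arm incidence: the endpoint does not include sludge, so this would over-correct.

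The cost is a small addition to the data form, on an organ already removed, and one line in the report. The estimate will be imprecise with about 61 specimens and may include stones that ultrasound would never have shown. It should be settled before enrolment, because specimens not examined at surgery may not be recoverable. If the full protocol already provides for specimen examination, the change is only to record the result and use it.

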### Informed consent

In the informed consent patients will receive all the information about the study protocol, the confidential nature of personal data and will fill up a questionnaire before signing or refuse.

There will be not inconveniences caused to the patients. No incentives are planned for the patients regarding the operation or the follow-up. All the medical information obtained from the patients will be kept confidential among the research scientists conducting the study.

The patients will be free to withdraw from the study whenever they want without any obligation. The stopping rules will be applied also in case of newly discovered statistically significant advantages or disadvantages in one group.

### Finishing and reporting dates

The study will take approximately 1 – 3 years for the inclusion period. According to the number of gastrectomies managed monthly in all Centers, the duration of the inclusion period can be approximately 2 years to reach the number of about 122 enrolled patients.

An interim report is planned at the end of any completed follow-up period.

#### Primary aims of the study

The aim of the study is to compare the results of gastrectomy plus prophylactic cholecystectomy versus gastrectomy only in patients undergoing gastric cancer surgery with a curative intent, in terms of morbidity, mortality, operation time, hospital stay, postoperative pain, return to normal activity, quality of life, and development of biliary symptoms after 5 years from surgery.

The primary aims of our study will be:

A) To evaluate whether patients who had not a prophylactic cholecystectomy and developed cholelithiasis will eventually suffer from symptoms related to their gallstones and will need another surgical intervention 5 years after gastrectomy

B) To evaluate the incidence of cholelithiasis in patients who have undegone gastric surgery

C) To evaluate whether prophylactic cholecystectomy increases complications rate, operative time and postoperative stay.

The onset of any other complications will be recorded intraoperatively, postoperatively, at discharge, 4-months after surgery. Subsequently, visits will be scheduled every 6-months in first two years after surgery, and yearly thereafter till completion of the 5-year follow-up.

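### Three aims are called primary, but the alpha, power and 122 patients apply only to onset of cholelithiasis; aims A and C are unsized, and C's three outcomes inflate the error rate

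*Protocol article*

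**What the plan says.** The section Primary aims of the study opens with a general comparison of the two arms "in terms of morbidity, mortality, operation time, hospital stay, postoperative pain, return to normal activity, quality of life" and biliary symptoms. It then states "The primary aims of our study will be" and lists three, unranked:

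- **A:** "To evaluate whether patients who had not a prophylactic cholecystectomy and developed cholelithiasis will eventually suffer from symptoms related to their gallstones", and whether they will need another operation by 5 years.
- **B:** "To evaluate the incidence of cholelithiasis in patients who have undegone gastric surgery", the aim nearest to the outcome used for sizing.
- **C:** "To evaluate whether prophylactic cholecystectomy increases complications rate, operative time and postoperative stay".

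Power Calculations uses one outcome. "Gastrectomy with concomitant cholecystectomy was assumed to increase cholelithiasis-free survival from 80% to 100" (per cent), and on that basis 122 patients, 61 per arm, "are necessary to ensure an 80% power with an alpha of 5%, when using a two-sided log-rank test".

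The Tests section names chi-squared or Fisher's exact test for categorical variables and Mann-Whitney for continuous ones. For onset of cholelithiasis it names Kaplan-Meier curves with a log-rank test and Cox regression. One level covers them all: "Significance level will be set at 5" (per cent).

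**The concern.** The word primary should mark the outcome that carries the stated error rate and power. Here it marks three aims, and only B, read as the between-arm comparison of stone onset, has either.

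Two consequences follow for the report:

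- Any of C's three outcomes can be presented as a primary result at an unadjusted 5%.
- A and C can be read as questions that the trial was built to answer. For A, a proportion among a handful of patients could pass as a firm estimate. For C, a non-significant difference could pass as evidence that adding cholecystectomy does no harm. The Conclusion section already says that dangerous complications are not expected in the treatment group, which makes that misreading easy.

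**Working it through.** **1. The plan's own figure.** Inputs from Power Calculations: 5-year stone-free proportion 80% vs 100%; overall survival 50% at 5 years; accrual 2 years; minimum follow-up 3 years; two-sided alpha 0.05; power 0.80. Exponential hazards are assumed.

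- Stone hazard in controls: −ln(0.80)/5 = 0.0446 per year. Death hazard: ln(2)/5 = 0.1386 per year. Sum: 0.1833.
- Probability that a control patient has an observed stone, averaged over follow-up of 3 to 5 years: (0.0446/0.1833) × [1 − mean of exp(−0.1833 f)] = 0.2435 × (1 − 0.483) = 0.126.
- Events needed (Freedman, hazard ratio 0): (1.960 + 0.842)² = 7.85.
- N = 7.85 / (0.126/2) = 125, against the stated 122. Power at 122 is 0.79.
- A Lakatos-type calculation on the same inputs gives N = 115 to 117 and power 0.82 at 122.

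The stated 122 is therefore reproduced closely, and it belongs to onset of cholelithiasis alone.

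**2. Aim A: how many patients it rests on.** Expected control patients with stones: 61 × 0.126 = 7.7, about 8. Two variants use other statements in the article:

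- 50% loss within 3 years gives a probability of 0.1075, and 61 × 0.1075 = 6.6.
- A full 5 years of follow-up for everyone gives 0.2435 × (1 − 0.80 × 0.50) = 0.146, and 61 × 0.146 = 8.9.

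So A has roughly 7 to 9 patients. As an illustration, 2 of 8 symptomatic (25%) has an exact 95% CI of 3% to 65%.

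**3. How many primary tests there are.**

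| Aim | Nature | Between-arm tests |
|---|---|---|
| A | one arm, conditional on stones, no null value or test stated | 0 |
| B | log-rank on stone onset | 1 |
| C | complications, operative time, stay | 3 |

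- Four tests at 5%: 1 − 0.95⁴ = 18.5% if independent; upper bound 4 × 5% = 20%.
- C alone: 1 − 0.95³ = 14.3% if independent; upper bound 15%.

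B adds little in practice. Its 0% incidence follows from removing the gallbladder, so its null hypothesis is hardly in doubt. The realistic exposure is C's 14.3%. Positive correlation among the outcomes lowers these figures, and perfect correlation would bring them to 5%.

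**4. Aim C: power with 61 per arm.** The article gives no complication rates, so these pairs are assumptions (two-proportion test, two-sided 5%):

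| Control vs cholecystectomy | Power | n per arm for 80% |
|---|---|---|
| 10% vs 15% | 13% | 686 |
| 20% vs 30% | 25% | 294 |
| 20% vs 40% | 68% | 82 |

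**5. Cost for B of keeping several primary tests.** With alpha split in three (0.0167 each), B needs about 163 (122 scaled) to 167 patients (Freedman), or has about 65% power with 122. Split in four (0.0125 each), it needs about 173 to 178.

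**The case against.** The confirmatory analysis can be identified: Power Calculations ties alpha, power and N to cholelithiasis-free survival, and Tests names onset of cholelithiasis as the survival endpoint. On that view the fault is a loose label. A multiplicity rule may also stand in an analysis plan that is not shown, and its absence from an article is no defect. Both points have weight, and the finding does not rest on a missing multiplicity rule. What remains is fixed in the article itself: three aims are called primary, and one of them was sized.

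A reader might infer more than the text supports:

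- *That each aim is tested at 5% and any of them could yield a positive primary result.* A has no stated test and nothing to reject. C asks about increases, so the significant result it looks for would show harm. Only B tests a benefit.
- *That the error rate is 14% because there are three aims.* One test per aim is the wrong count: A has none and C has three. The 14.3% above is for C's three outcomes.
- *That it is 34%, for the eight outcomes in the opening sentence (1 − 0.95⁸).* That sentence states the general aim. Mortality, pain, return to normal activity and quality of life do not appear by name in A to C, and the eight leave out stone onset, the one sized endpoint.

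A further objection is that making B the sole primary confirms a near-certain result and demotes A, the more useful clinical question. That is fair. It is a reason to let the sponsor choose the primary endpoint and restate its power. It does not justify calling A primary on about 8 patients.

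**Conclusion.** The point holds as a mismatch between label and design. The stated 5% alpha, 80% power and 122 patients belong to aim B only. A is a one-arm estimate on roughly 7 to 9 patients. C brings three harm outcomes at an unadjusted 5% and, for complications, low power unless the increase is very large.

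The familywise error over the four between-arm tests is 18.5% under independence and at most 20%, and most of it sits in C. The patient count for A assumes constant hazards and the plan's own stone and survival rates. The power for C rests on assumed complication rates.

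The larger practical risk is over-reading an imprecise A, or a non-significant C, as an answer from a powered primary comparison.

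**What to change.** In Primary aims of the study, name one confirmatory primary endpoint, tested at two-sided 5%. Onset of cholelithiasis is the sized one and keeps N at 122. If the sponsor prefers another, its power should be restated.

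Then:

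- Report aim A as the proportion of control patients with stones who develop symptoms or need surgery, with an exact 95% CI, and state in advance that it will rest on about 8 patients.
- Make aim C's complications, operative time and stay secondary, reported as between-arm differences with 95% CIs. Add a sentence to Tests saying that non-significance will not be read as no increase.

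The cost is relabelling the aims and a sentence or two in Tests, with no extra patients if the sized endpoint is kept. The downside is that A and C can no longer be claimed as primary results.

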## Conclusion

Gallbladder disease is common after gastrectomy for cancer. Any improvement in this field will benefit many patients improving their quality of life and reducing morbidity, mortality, and hospital stay. Complications from cholecystectomy during another abdominal procedure are known to be minimal. The treatment group is not expected to experience dangerous complication because concomitant cholecystectomy is a very simple procedure. On the other hand, theoretic advantages will be represented by the avoidance of reintervention for cholelithiasis only.

All our patients will be informed about the study and an informed consent will be obtained. According to the best of our knowledge, there will not be any additional inconveniences caused to the patients. All the medical information obtained from the patients will be kept confidential among the research scientists conducting the study. The patients will be free to withdraw from the study, whenever they want without any obligation.

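### Primary aim C (complications, operative time, stay) is assigned unadjusted difference tests in a trial sized only for cholelithiasis; adjusted estimates with 95% confidence intervals would serve it better at little cost

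*Protocol article*

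**What the plan says.** The section Primary aims of the study lists three primary aims, A to C. Aim C reads "To evaluate whether prophylactic cholecystectomy increases complications rate, operative time and postoperative stay". It names no target difference and no largest acceptable increase.

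The Power Calculations section sizes the trial on a different outcome. It states "Gastrectomy with concomitant cholecystectomy was assumed to increase cholelithiasis-free survival from 80% to 100" per cent. The resulting total is "122 patients (61 in the control group and 61 in the cholecystectomy group"). The section then explains that these numbers "are necessary to ensure an 80% power with an alpha of 5%, when using a two-sided log-rank test". It gives no complication rate, and no standard deviation for operative time or stay.

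The Tests section assigns chi-squared or Fisher's exact test to categorical variables and "the non-parametric Mann-Whitney U-test for continuous variables", at the 5% level. Its only multivariable model is a Cox regression, named together with the cholelithiasis curves.

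The operations are varied: "The standard surgery for gastric cancer includes both total and subtotal gastrectomy with lymphadenectomy (D1, D2, D3), either laparoscopic or laparotomic". The Data Collection section lists gastrectomy type, extent of lymphadenectomy and reconstruction among the operative data. The Randomization section describes one central ordered list, mentions no stratification, and has the allocation passed to the operating surgeon.

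On expected harm, the Conclusion says: "The treatment group is not expected to experience dangerous complication because concomitant cholecystectomy is a very simple procedure".

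**The concern.** Whether to add the procedure depends on weighing biliary disease avoided against perioperative harm. The protocol takes the rate of cholelithiasis after cholecystectomy to be zero, so the comparison that sized the trial carries little uncertainty on that side. The harm question has no sample-size support, and the tests assigned to it yield a p-value for a difference and nothing about how large an increase remains possible.

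Two things are at stake:

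- **Interpretation.** A non-significant test on 61 per arm is compatible with a clinically relevant excess of complications. The protocol already expects little harm, so such a result could easily be taken as reassurance.
- **Precision.** Total versus subtotal gastrectomy and open versus laparoscopic approach can be expected to influence operative time, stay and complications. A comparison that ignores them is noisier than it need be, and any chance imbalance between the arms stays in the estimate.

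**Working it through.** **1. The plan's own figure.** Inputs from Power Calculations: 5-year cholelithiasis 20% versus 0%; "Assuming a constant accrual rate and an accrual time of 2 years, a minimum follow-up period of 3 years" (5 years in total); 50% survival at 5 years; two-sided 5%; 80% power.

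- Control hazard: λ₁ = −ln(0.8)/5 = 0.0446. Treated hazard: λ₂ ≈ 0. Average: λ̄ = 0.0223. Loss hazard: −ln(0.5)/5 = 0.1386.
- Probability of an observed event, with uniform accrual over 2 years: 0.126 at λ₁ and 0.0655 at λ̄.
- With φ(λ) = λ²/P(event): N = [1.96·√(4φ(λ̄)) + 0.842·√(2φ(λ₁) + 2φ(λ₂))]² / (λ₁ − λ₂)² = (0.342 + 0.150)² / 0.00199 ≈ 121.3, or 122 in whole patients with equal arms.

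The stated 122 is reproduced from cholelithiasis alone. Aim C plays no part in it. Loss over the years hardly touches perioperative outcomes, so 61 per arm is the right base below.

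**2. Complications.** The control rate p is not in the document. I assume 10% to 30%.

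- Half-width of the 95% interval with no observed difference: 1.96·√(2p(1−p)/61). At p = 0.20 this is 1.96·√(0.32/61) = 0.142.
- Power for an increase d: Φ{[d − 1.96·√(2p̄(1−p̄)/61)] / √([p₁(1−p₁) + p₂(1−p₂)]/61)}, where p₁ and p₂ = p₁ + d are the rates in the two arms and p̄ is their mean. At p₁ = 0.20 and d = 0.10: (0.100 − 0.154)/0.0779 = −0.69, so power is 25%.

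| Assumed control rate | 95% CI half-width | Increase detectable with 80% power | Power for +10 points (exact Fisher) |
|---|---|---|---|
| 10% | ±10.6 points | +20 points | 34% (25%) |
| 20% | ±14.2 points | +23 points | 25% (19%) |
| 30% | ±16.3 points | +25 points | 21% (16%) |

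Across this range a true 10-point increase would be missed about two times in three or more often.

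**3. Operative time and stay.** No SD is given, so results are in SD units.

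- Detectable difference: (1.96 + 0.842)·√(2/61) = 0.51 SD. With Mann-Whitney on normal data (relative efficiency 0.955) it is 0.51/√0.955 = 0.52 SD.
- With adjustment, multiply by √(1 − R²). R² is also an assumption: 10% gives 0.48 SD, 30% gives 0.42 SD, 50% gives 0.36 SD.

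**4. Chance imbalance.** Assume that a share s of patients has total gastrectomy and that the list is unstratified. The between-arm difference has SE √(2s(1−s)/61). At s = 0.40 the SE is 0.089, and the probability of an imbalance of 10 points or more is 2·[1 − Φ(0.10/0.089)] ≈ 26%. For s from 30% to 50% it runs from 23% to 27%.

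**The case against.** Four arguments can be made against this point.

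- **The protocol makes no claim of safety from non-significance.** A reader might infer from the Conclusion that p > 0.05 will be declared proof of no added harm. The document does not say so. Aim C asks whether there is an increase, and a difference test addresses that question, though with low power. The statements about low risk are background expectation, not a decision rule. This stands. What remains is that the tests alone cannot answer the question in the negative.
- **Unadjusted tests are not an error.** A reader might infer bias from the mix of operations. Under randomisation the comparison is unbiased and type I error is controlled. Adjustment is a gain in precision and would not rescue the inference on complications. This also stands.
- **Much of this belongs to an analysis plan.** Covariates and confidence intervals are often left to a document not shown here, and their absence alone would be no finding. The point therefore rests on what the article does fix: the named tests for these outcome types, and a multivariable model named only for cholelithiasis. Nothing in the article rules out further analyses.
- **The sizes rest on assumptions.** It is tempting to give 14 to 15 points as the excess that the trial can exclude, but that holds only for control rates of 20% to 25% and no observed difference. An R² of 30% to 50%, worth 1/(1 − R²) = 1.43 to 2.0 times the patients, has no basis in the document. Without an SD, it cannot be settled whether 0.5 SD would miss a relevant increase in time or stay.

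A formal margin is not a ready answer either. The protocol gives none. At an illustrative 10-point margin (one-sided 2.5%, equal true rates), 80% power needs 142, 252 or 330 patients per arm at control rates of 10%, 20% or 30%. With 61 per arm the power is 45%, 28% or 22%.

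**Conclusion.** The point holds as a worthwhile and inexpensive improvement, not as a flaw in validity. Aim C is primary, the trial was not sized for it, and the tests that the article assigns to its outcomes are unadjusted tests of difference. By themselves they cannot show absence of an increase. At 61 per arm the interval for the complication difference extends about 11 to 16 points either side of zero, and the detectable difference in operative time or stay is about 0.5 SD. The first range depends on an assumed control rate of 10% to 30% and no observed difference; the second assumes 80% power and roughly normal data. Adjustment would narrow the second figure to 0.48 to 0.42 SD if the covariates explain 10% to 30% of the variance. It would also protect against an imbalance in gastrectomy type that has roughly a one-in-four chance of reaching 10 points.

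**What to change.** For aim C:

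- Report the risk difference in complications and the differences in operative time and stay, each with a 95% confidence interval.
- Adjust for gastrectomy type (total or subtotal) and approach (open or laparoscopic), both as planned and recorded before the allocation is disclosed. The operating surgeon learns the allocation, so the procedure actually performed is a less safe covariate. Add centre where centre sizes allow. Keep the covariate set small: at overall complication rates of 10% to 30%, 122 patients give only about 12 to 37 patients with a complication.
- Keep the rank tests as a companion analysis for skewed outcomes such as stay.
- State that a non-significant result will not be read as absence of an increase.
- Give the excess that the trial could exclude as a range tied to the assumed control rate (about 11 points at 10%, 14 at 20%, 16 at 30%, with no observed difference), not as one fixed figure.

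The cost is slightly more analysis work, a record of the planned procedure and approach before allocation, and a more modest conclusion on safety. No extra patients are needed.
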